### Secondary research questions

1. Is pulsed radiofrequency of DRG effective for pain relief - measured as a decrease in VAS, measured at 4 weeks?

2. Is application of PRF associated with any short-term (at 4 weeks) or long-term persisting (beyond 3 months) side effects?

3. Is there any improvement in Oswestry Disability Index (ODI) in patients of CLR after PRF; measured at 4 weeks, 2 months, and 3 months?

4. Is there any decrease in analgesic (medications) use in patients with CLR after application of PRF; measured at 1 week, 4 weeks, 2 months, and 3 months?

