### Duration of treatment and follow-up

Duration of treatment period will involve approximately 30 to 60 min of actual intervention done in the OR. The duration of complete follow-up will be for 3 months after the intervention with the following interval follow-up assessments: (1) 30 min post-procedure in recovery, (2) 24 h after - by a phone call (only VAS and side effects); (3) at 1 week post-procedure visit to the assessor (VAS, ODI, medications, side effects); (4) at 4 weeks post-procedure visit to the observer for assessment for success (VAS, ODI, medications, side effects); (5) at 2 months post-procedure-visit to observer (VAS, ODI, medications, side effects); (6) at 3 months post-procedure visit to the observer - last follow-up visit (VAS, ODI, medications, side effects).

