#### Secondary

1. Effectiveness of PRF treatment of DRG, when compared to placebo, as a treatment in patients with CLR: outcome measured as decrease in VAS scores (0 to 10) from baseline measured at recruitment. For definition of success we would consider at least 50% decrease in VAS scores assessed at 4 weeks.

2. Assessment of short-term side effects: percentage of patients having side effects after PRF treatment assessed at 1 week, compared with the placebo group. Assessment of persisting side effects: percentage of patients having side effects after PRF treatment, beyond 1 week, compared with placebo group. Short-term side effects (within 1 week – recorded at the first visit):

Nausea

Headache

Transient increase in pain

Fever (temperature in°C)

Transient paresis/paraesthesia

Dysesthesia

Long-term side effects (persisting side effects assessed at visits 1 week and at 6 weeks):

Infection at the site

Meningitis

Epidural abscess

Hyposensibility

Paralysis/paresis

Dysesthesiae

Any other

3. Improvement in ODI: success defined as at least 50% improvement (or decrease) in ODI measured at 4 weeks, compared with placebo group.

4. Decrease in the analgesic medications used: percentage of patients with increase or decrease in their medication use (either in dose, frequency), compared with placebo group.

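### The short-term and persisting side-effect windows contradict each other and the visit schedule, and only one version of the persisting outcome can be tabulated.

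*Protocol article*

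**What the plan says.** Three places in the protocol article set the timing of side effects.

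- **Secondary research questions, item 2** asks: "Is application of PRF associated with any short-term (at 4 weeks) or long-term persisting (beyond 3 months) side effects".
- **Primary and secondary outcome measures, Secondary, item 2** defines the short-term outcome as the "percentage of patients having side effects after PRF treatment assessed at 1 week, compared with the placebo group". It defines the persisting outcome as the percentage with side effects later than 1 week. Two event lists follow. The short-term list is for effects within 1 week, recorded at the first visit. The other list is headed "Long-term side effects (persisting side effects assessed at visits 1 week and at 6 weeks".
- **Duration of treatment and follow-up** states: "The duration of complete follow-up will be for 3 months after the intervention". After the 30-minute recovery check, the 24-hour contact is "by a phone call (only VAS and side effects". The next visits are "at 1 week post-procedure visit to the assessor (VAS, ODI, medications, side effects" and "at 4 weeks post-procedure visit to the observer for assessment for success (VAS, ODI, medications, side effects". A 2-month visit collects the same items, and the series closes "at 3 months post-procedure visit to the observer - last follow-up visit".

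**The concern.** Comparing side effects between pulsed radiofrequency and placebo is a stated secondary objective. The Discussion says the assessment is there to show which risks need further study and need to be explained to patients. To serve that purpose, each reported percentage needs one numerator definition, and that definition has to point at times when patients are seen.

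As written, the class of an event depends on which section the analyst follows, and part of the research question asks about a period in which nobody is observed. The Trial status section reports 28 of 32 interventions done. If the window is chosen only at analysis, it could be chosen with results by arm in view.

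**Working it through.** The plan gives no sample-size, power or alpha figure for this outcome, so the check sets each stated window against the schedule.

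**Scheduled contacts in days** (taking a month as about 30.4 days): 30 min = day 0; 24 h = day 1; 1 week = day 7; 4 weeks = day 28; 2 months ≈ day 61; 3 months ≈ day 91, the last contact.

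**Each window against the schedule**

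| Class | Where stated | Window | Matching contacts |
|---|---|---|---|
| Short-term | Research question, item 2 | 4 weeks | 4-week visit |
| Short-term | Outcome item 2, sentence and list heading | 1 week | 1-week visit, covering the first week |
| Persisting | Research question, item 2 | later than 3 months | none |
| Persisting | Outcome item 2, sentence | later than 1 week | 4 weeks, 2 months, 3 months |
| Persisting | Outcome item 2, list heading | 1 week and 6 weeks | 1 week only; none at 6 weeks |

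**The 6-week point.** 6 × 7 = day 42. That is 42 − 28 = 14 days after the 4-week visit and about 61 − 42 = 19 days before the 2-month visit. No scheduled visit can reasonably stand in for it.

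**The window after 3 months.** It begins at about day 91, when follow-up ends, so it has no scheduled observations.

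**How single events are classed**

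| Effect present only at | Research question | Outcome sentences | Long-term list heading |
|---|---|---|---|
| 1 week | not short-term if 4 weeks is a point; short-term if it means up to 4 weeks | short-term | a long-term assessment time |
| 4 weeks | short-term | persisting | not an assessment time |
| 2 months | neither | persisting | not an assessment time |
| 3 months | neither (not later than 3 months) | persisting | not an assessment time |

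No row gets the same answer from all three statements. Item 2 of the outcomes also disagrees with itself: effects defined as later than 1 week are to be assessed partly at 1 week, the visit that already serves the short-term outcome.

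**Size of a reclassification.** The planned total is 32 with 1:1 allocation. Assuming an even split, 32 / 2 = 16 per arm. Moving one patient between classes changes that arm's percentage by 1/16 = 6.25 points.

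**The case against.** The strongest reply is that no data are lost. The schedule collects side effects at 24 hours and at every visit from 1 week to 3 months, and the outcome sentence for persisting effects can be applied to those visits directly. That stands, and it limits the point. A reader might infer that no persisting outcome can be produced at all, or that the 4-week, 2-month and 3-month data belong to no defined outcome. The documents do not support either reading: all three visits fall later than 1 week, and the percentage can be tabulated from them. What cannot be produced are the 6-week version and the version after 3 months.

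It could also be said that the 6-week entry is a leftover from another schedule, or that a full protocol settles the matter. The first may be true, but the text still names a visit that does not exist. The second does not excuse the conflict, because the article itself publishes incompatible values and is not merely silent.

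Two further criticisms are tempting but do not belong here. With about 16 patients per arm, a rate of zero events would be imprecise. That is true under any window and follows from a sample size set on feasibility grounds. The short-term list has no catch-all entry, but the long-term list has one and is also tied to the 1-week visit, and the schedule collects side effects without restriction.

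Finally, the primary outcomes are recruitment and completion, and nothing here touches them. That is right, and it sets the severity.

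**Conclusion.** The contradiction is confirmed from the article's own text. There are two short-term windows and three persisting windows. Of the persisting windows, one (later than 3 months) has no scheduled observation, one (1 and 6 weeks) has none at its later time point and overlaps the short-term class at its earlier one, and one (later than 1 week) can be tabulated. The long-term part of the research question cannot be answered as worded.

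The consequence is an ambiguous classification of events, at 6.25 percentage points per reclassified patient if arms are 16 each. How many patients would change class depends on the event data and cannot be estimated from the documents.

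Severity: should-fix. This is a secondary safety outcome in a feasibility pilot, and the recruitment, completion, pain and disability outcomes are unaffected.

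**What to change.** Before any unblinded analysis, reconcile item 2 of the research questions, item 2 of the secondary outcomes and the visit schedule to one pair of windows, both defined by when an effect is reported. For example:

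- **Short-term:** any side effect reported at any contact up to and including the 1-week visit.
- **Later:** any side effect reported at the 4-week, 2-month or 3-month visit, with effects continuing from week 1 shown separately from those newly reported.

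State that a patient may count in both classes. The single basis matters. If short-term were defined by onset and later by presence at a visit, an effect starting on day 10 and resolved before week 4 would fall in neither class, and a new effect at 2 months would be called persisting.

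Delete the 6-week time point from the list heading. Restate the long-term part of the research question as side effects up to, or present at, the 3-month visit.

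The cost is wording only, because the listed contacts already collect the data. The price is that the trial then makes no claim about side effects after 3 months, which its schedule could not support in any case.

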### Rationale behind the assessment of interventions for success at 4 weeks

1. Four weeks can be considered as the optimum time at which the therapeutic effect of PRF would be at its maximum.

2. There is a theoretical possibility of local anesthetic action in either group, which can be eliminated at 4 weeks.

3. Even if there has been a placebo effect it is important to know whether it is sustained at 4 weeks, in comparison to the actual treatment effect.

4. To allow appropriate time for a decrease in ODI (functional assessment) to happen as a result of decreasing pain.

### Trial design, outline, and flow chart

#### Sample size, recruitment rate

Sample size has been determined based on feasibility considerations. Total duration of recruitment planned is 8 (clinically active) months. The proposed target is recruitment for 8 months, with an expectation of at least four patients every month, with a total of 32 patients for the study. Potential to recruit patients, as four patients every month has been calculated based on the transforaminal steroid injections (TFESI) performed in the last 3 to 6 months and booked for the next 3 to 6 months (calculated as monthly) at St Joseph’s Healthcare; data obtained from St Joseph’s Healthcare, Department of Anesthesia and Pain. TFESI represents a well-accepted, presently performed intervention for patients of CLR and most patients suitable for that are potential recruits for this study.

#### Randomization

Patients will be randomly allocated to each group using a 1:1 ratio. The allocation will be done in blocks using block sizes of 2, 4, and 6.

#### Statistical tests

The characteristics of the trial participants will be described using mean (standard deviation) or counts as appropriate. We will use a flow diagram to summarize the flow of patients in the trial. Feasibility outcomes will be reported as counts (proportions).

## Discussion

The results of this pilot study would primarily give us information about the patient recruitment and study methodology. This is being done as there are no previous studies (RCTs) to indicate the successful effects of PRF in CLR. The initial study proposal was to conduct an RCT comparing PRF-DRG with TFESI, which have proven to be more successful than midline ESIs for lumbar radiculopathy [52], and are probably the most effective intervention available. However our literature search showed that so far, there were no RCTs involving sufficient participant numbers to evaluate the efficacy of PRF. The only RCT by Van Zundert *et al.*[16] on cervical radicular pain had only 19 participants in either group. Keeping this in mind we devised this proof of concept study to evaluate the efficacy of PRF as compared to placebo.

It is very challenging to devise and conduct a placebo controlled trial in interventional pain medicine. Because of the nature of the problem, which involves significant suffering for a long time, patients may be unwilling to participate as blind participants. CLR patients would have had a trial of most medications and simple interventions before they go on to have complex spinal interventions, such as PRF-DRG. It may also be difficult to have such patients to be under long periods of follow-up after a blind intervention, especially if it is not of benefit to the patient. This trial would be able to tell us whether we were able to recruit patients as expected for the trial and also whether they continue to be participants of the study for the whole duration. The other important and novel aspect of this study which merits attention is the technique of patient blinding during the procedure. Although we will not be formally evaluating the blinding process, it will be interesting to know if we faced significant challenges and if such a methodology needs to be appropriately modified for a future trial. The study would also assess the outcomes of pain relief from PRF compared to placebo. Apart from telling us if PRF is successful, the study would also indicate the difference in pain relief in terms of absolute reduction in VAS scores. This is necessary to assess the number of study participants for a future trial. The assessment of side effects is included to understand if there are major or minor side effects and risks which need to be better studied and informed to the patients.

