
In this ‘proof of concept’ study we would like to answer the question, ‘whether PRF, when compared to placebo, is effective in reducing pain in chronic lumbar radiculopathy (CLR)’? With this rationale and purpose, a feasibility study is being done to assess whether a larger scale clinical study with the same methodology can be done. This pilot study would also help in assessing the actual number of patients to be involved in the larger clinical study to give a statistically significant difference. With positive outcomes (treatment success), we could also determine the length of follow-up necessary in a full-scale clinical study in order to study the duration of effects.

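### About 16 patients per arm, chosen on feasibility alone, cannot reliably tell whether PRF works or supply the observed VAS difference for sizing the main trial

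*Protocol article*

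**What the plan says.** The article gives the pilot's efficacy data two jobs beyond feasibility.

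- **Judging the treatment.** Discussion: "Apart from telling us if PRF is successful, the study would also indicate the difference in pain relief", expressed as absolute reduction in VAS.
- **Sizing the next trial.** The sentence that follows in the Discussion is "This is necessary to assess the number of study participants for a future trial". The closing paragraph of the Background (end of Systematic reviews) puts it more softly: the pilot would "help in assessing the actual number of patients to be involved in the larger clinical study to give a statistically significant difference".

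The number of patients has a different origin. Under Sample size, recruitment rate: "Sample size has been determined based on feasibility considerations"; the plan is 8 months of recruitment "with an expectation of at least four patients every month, with a total of 32 patients for the study". Under Randomization: "Patients will be randomly allocated to each group using a 1:1 ratio". Effectiveness is a secondary outcome, "outcome measured as decrease in VAS scores (0 to 10) from baseline measured at recruitment", with success defined as a fall of at least 50% at 4 weeks. No alpha, power, SD or target VAS difference is stated.

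**The concern.** A sample size taken from recruitment capacity is proper for a feasibility study. The difficulty is the use then made of the effect estimate. Required sample size varies with the inverse square of the assumed difference, so a noisy difference becomes a much noisier sample size. A statement that the study will show whether PRF is successful also claims a property that a trial of this size has only if the effect is very large.

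The article applies the stricter standard elsewhere. The Background names too few subjects as the main limitation of the sham-controlled cervical trial, which Table 3 gives as 11 and 12 patients. The Discussion gives the same trial as 19 per group and still treats it as insufficient to evaluate efficacy. On either figure it is of the same order as this pilot.

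At stake are a main trial that is too small or needlessly large, and readers who take a pilot estimate as an answer on efficacy.

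**Working it through.** **The plan's own figure.** 8 months × 4 patients = 32, which reproduces. At 1:1 this is 16 per arm. There is no power calculation to reproduce.

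**Assumptions, since the article gives none.** Two-sided alpha 0.05, main-trial power 80%, SD of the VAS outcome 2 to 3 points, true difference δ of 1 to 2 points, no dropout. Dropout would make precision worse.

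**1. Precision of the pilot difference.** SE = SD × √(2/16); half-width = t(0.975, 30 df) × SE = 2.042 × SE.

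| SD | SE | 95% CI half-width |
|---|---|---|
| 2 | 0.71 | 1.44 |
| 2.5 | 0.88 | 1.81 |
| 3 | 1.06 | 2.17 |

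At SD 2.5, an observed difference of 1.5 has a 95% CI of about −0.3 to 3.3.

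**2. Power of the pilot itself (t-test).** For δ = 1 / 1.5 / 2: 28% / 54% / 78% at SD 2; 20% / 38% / 59% at SD 2.5; 15% / 28% / 45% at SD 3.

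**3. Sizing the main trial on the pilot.** Required n per arm = 2 × [(1.960 + 0.842) × SD/δ]². Examples: SD 2, δ 2 gives 15.7; SD 2.5, δ 1.5 gives 43.6; SD 3, δ 1 gives 141.3. Pilots were simulated with 16 per arm. The observed difference and SD were put into the same formula, and the true power of the resulting trial was computed. The size of the observed difference was used whatever its sign, and n was not rounded.

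| SD, δ | n per arm needed | Middle half of n per arm from pilots | Main trials with power under 50% |
|---|---|---|---|
| 2, 2 | 16 | 10 to 27 | 15% |
| 2.5, 1.5 | 44 | 21 to about 119 | about 25% |
| 3, 1 | 141 | 45 to 510 | 36% |

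Over all nine combinations of SD 2, 2.5, 3 and δ 1, 1.5, 2, the last column runs from 15% to 36%.

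*Hand check, ignoring error in the SD.* True power falls below 50% when the observed difference exceeds (2.802/1.960) × δ = 1.43δ in size. At SD 2, δ 2: P(Z > 0.43 × 2/0.707) = P(Z > 1.21) = 11%. At SD 3, δ 1: P(Z > 0.43/1.06) = 34%, plus about 1% with the wrong sign, so 35%. Error in the SD raises these to the simulated values.

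*Convention.* Keeping only pilots with a positive difference and rounding n up gives 11% at SD 2, δ 2 and 37% at SD 2.5, δ 1. The conclusion does not depend on this choice.

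**4. The 50% responder outcome.** Fisher exact power, 16 per arm, using rates cited in Table 3. Sham rates (25% to 33%) are from the cervical trial.

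| PRF rate and source | vs sham 33% | vs sham 25% |
|---|---|---|
| 49.5% (52/105, uncontrolled lumbar series) | 8% | 18% |
| 70% (lumbosacral pilot RCT, no sham arm) | 42% | 62% |
| 82% (cervical sham-controlled RCT) | 72% | 87% |

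These rates were read at 2 or 3 months, not 4 weeks, and not all use the same definition of success, so they are indicative only.

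**The case against.** The case on the other side has several parts.

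- **Feasibility is the primary aim.** Effectiveness is secondary, Statistical tests describes only descriptive and feasibility reporting, and the Discussion opens by saying the pilot mainly informs recruitment and methodology. This stands, and it limits the point to the claims made for the secondary data.
- **The sizing method is not fixed.** The Background says only that the pilot will help, and neither place gives a formula or excludes a clinically important difference. This stands in part: the Discussion does name the observed VAS difference as the quantity needed.
- **A large effect would be detected.** At 82% against 25% to 33%, power is 72% to 87%. That is correct, but the contrast comes from the 23-patient cervical trial that the article itself calls too small. A reader might take only the lowest row and infer that responder power is 8% to 18%. The article's own rates do not support so narrow a range.
- **No efficacy gate is stated.** A reader might infer that a chance null result would stop a useful treatment, or that only a promising pilot would lead on and so inflate the estimate. The documents do not support this. The stated criteria for success are four patients per month and 80% of eligible patients recruited, and the remark about positive outcomes in the Background concerns length of follow-up.
- **Little can change now.** Trial status reports 28 of 32 treated. The remedy needs no further patients.

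**Conclusion.** The concern holds in a limited form. The Discussion, and more softly the Background, asks the pilot to show whether PRF is successful and to supply the observed difference for sizing the main trial. About 16 per arm cannot do either reliably.

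Under assumed SDs of 2 to 3, the difference is known only to within 1.4 to 2.2 VAS points. In every scenario examined, sizing on the observed result leaves 15% to 36% of main trials with less than an even chance of detecting the true effect. Even the most favourable scenario (SD 2, difference 2) gives 10 to 27 per arm for the middle half of pilots, where 16 are needed. Responder power of 8% to 87% shows how far any efficacy conclusion depends on which cited rate is believed.

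The SD and true difference are assumptions, and the picture would be better only if the effect were about one SD or more. A reader might also infer that the article plans a formal efficacy verdict. It states no efficacy test or decision rule, so the fault lies in what is claimed for the data. The primary feasibility aim, the design and the choice of 32 for feasibility are unaffected.

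**What to change.** 1. State that the main trial will be sized on a prespecified clinically important VAS difference, not on the difference observed in the pilot.
2. Take from the pilot only the SD, the sham response and the dropout rate. Use the SD with a conservative allowance, such as an upper confidence limit. The one-sided 80% limit with 30 df is √(30/χ²(0.20, 30)) = 1.13 times the observed SD; other choices are acceptable if fixed in advance.
3. Report the pilot's VAS and responder effects as estimates with 95% confidence intervals.
4. In the Discussion, replace the statement that the study will tell whether PRF is successful with wording to the effect that it estimates the difference, without a claim of efficacy. Align the closing paragraph of the Background with this.

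The cost is wording only, with no change to recruitment, conduct or the primary outcomes. The drawback is a more modest statement on efficacy.
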